### Trial Delivery

The trial will be delivered using a custom-designed website that will contain the 2 web-based programs. This website will allow self-report assessments, intervention materials, and email reminders to be delivered seamlessly to the participants. Furthermore, the website will collect and securely house the survey data collected. To streamline access and reduce the need for participants to create log-ins while maintaining security and confidentiality, participants will only need to provide an email to access the program.

If surveys or the program are discontinued, participants will be emailed a single reminder (at 48 hours if they discontinue any part of the preintervention, program, and postintervention survey and 1 week for the 6-month follow-up survey) with a unique link to access the program from their email account to continue from where they left to complete that part of the study. We expect most participants will complete the preintervention, program, and postintervention surveys in one 40-minute sitting. As such, we do not anticipate that these reminders will be needed frequently; however, given that people could discontinue the program or surveys, we have a method to reconnect them with the study.

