#### Participant Recruitment and Informed Consent

Participants will be recruited on the web through participating workplaces. To be eligible for the trial, potential participants must fulfill the following criteria:

Be an employee in a participating Australian workplaceBe aged ≥18 years, living in Australia, and fluent in reading and understanding EnglishHave access to a device (eg, desktop, laptop, tablet, or smartphone) and a reliable internet connection

If participants complete the abovementioned screening criteria and are not eligible, they will be informed and provided with a list of relevant help-seeking resources.

After being assigned a condition, the workplace will send a brief email or SMS text message to their employees inviting them to participate in the trial (refer to the Randomization section for an example). The email or SMS text message will contain a link to the web page containing information about the study. Then, the employees who click the link provided by their employers will be taken to the information and consent web-based page, where they will be invited to read the information that the study and provide their consent to participate in the study on the web. This process will be confidential, and their work organization will not be informed of who among their employees has consented to participate in the trial. Participants can complete the preintervention, program, and postintervention survey in a single session. Furthermore, participants can save their progress at the bottom of the screen if they wish and re-enter the survey or program at the last point they left off by reaccessing the link from their email or SMS text message. In addition, they will be sent reminders to complete the program if they have not done so within the expected time frames (Figure 1).

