#### Secondary Outcomes

Effectiveness will be compared between the Helipad co-designed interactive program condition and the standard psychoeducation web-based program condition for mental illness stigma, mental health literacy, and help-seeking attitudes (hypothesis 2), which will be assessed, respectively, based on reduced mental health stigma (Stigma and Self-Stigma Scales [40]), increased mental health literacy (Anxiety Literacy Questionnaire [A-Lit] and Depression Literacy Questionnaire [D-Lit] composite measure [41,42]), and increased help-seeking attitudes (Attitudes Toward Seeking Professional Psychological Help Scale-short form [43]) over time relative to the control condition.

In addition, we will examine the comparative effectiveness of the Helipad co-designed interactive program condition and the standard psychoeducation web-based program condition on reducing symptoms of mental ill-health and increasing quality of life and functioning (hypothesis 4). This will be determined based on reduced symptoms over time of depression (Patient-Reported Outcomes Measurement Information System [PROMIS] Depression short form scale [44]), anxiety (PROMIS Anxiety short form scale [44]), and general psychological distress (Distress Questionnaire-5 [DQ5] [45]) and increased scores on the Recovering Quality of Life (ReQoL-10) Questionnaire [46] and increased work and activity functioning (Work Productivity and Activity Impairment [WPAI] questionnaire [47]).

Finally, the relative effects of the program on increasing help-seeking behavior (hypothesis 3) will be assessed by the proportion of participants who reported seeking help from a professional source (defined as a psychologist or counselor, a psychiatrist, a family doctor or general practitioner [GP], or an EAP) in the past 6 months. We anticipate that this will be greater in the Helipad co-designed interactive program group among people with elevated symptoms of depression or anxiety relative to the control condition (standard psychoeducation only).

The primary end point for changes in mental health literacy is the posttest assessment, while for the other secondary outcomes, the 6-month follow-up assessment will be the primary end point as these outcomes take longer to elicit change.

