### Data Collection

#### Overview

Participants who agree to participate in the trial by clicking the link will be asked to provide an email address and complete a brief 10-minute baseline questionnaire. Following completion of the baseline questionnaire, participants will immediately be given access to the web-based program (approximately 20 minutes), which will be followed immediately by the 10-minute posttest questionnaire survey. The 10-minute follow-up survey link will be sent to participants via email 6 months after completion of their allocated condition.

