### Limitations and Risks

A potential but omnipresent risk in trials is that of recruitment; this risk involves recruiting insufficient participants to enable statistical power to detect intervention effects. We expect this risk to be moderate given that the Helipad trial is situated within a large clinical trials network (Mental Health Australis General Clinical Trials Network [64]), which will provide recruitment support through an extensive network and by directly providing contacts in workplaces. In addition, based on previous trials we have conducted, we have found that recruitment is typically highly successful in web-based trials, where we have previously engaged comparable number of participants [34-36], including in cluster-based universal web-based trials [37]. It may be challenging to retain the participants; however, given the instantaneous pre- and posttest design, attrition between these 2 time points may be less likely than in previous trials. Furthermore, as outlined in our data analysis plan, this risk is somewhat mitigated by conducting statistical analyses that account for all available data (ie, mixed effects models).

Moreover, there is an ethical risk that the intervention may provide information to participants that leads them to think they may be experiencing symptoms of common mental health problems (ie, psychological distress, anxiety, or depression). We intend to measure adverse events in our postintervention and 6-month follow-up surveys, which may capture these data. However, this forms a key part of the intervention, in that it is expected to prompt those who may not know they are experiencing symptoms of a common mental disorder to seek help. There is potential that such an experience may cause distress to a small proportion of people. We expect this risk to be low, as approximately 20% (180/900) of the participants are expected to have elevated symptoms, and this is unlikely to be surprising for many of these people. Given that the intervention is specifically designed to support this group, we will be providing specific resources, including how and where to seek treatment, to equip participants to access appropriate sources of help if this occurs.

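### The 6-month survey has a single email reminder at 1 week, may not remind people who never open it, and has no attrition allowance, although hypotheses 3 and 4 and the economic analysis depend on it

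*Protocol article*

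**What the plan says.** The 6-month survey is sent by email (Data Collection, Overview): "The 10-minute follow-up survey link will be sent to participants via email 6 months after completion of their allocated condition". An email address is the only contact detail mentioned; under Trial Delivery, "participants will only need to provide an email to access the program".

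Trial Delivery sets the reminder rule: "If surveys or the program are discontinued, participants will be emailed a single reminder". It goes out at 48 hours for the session made up of pre-survey, program and post-survey, and at "1 week for the 6-month follow-up survey". Its link lets people return "to continue from where they left to complete that part of the study". The other reminder text, under Participant Recruitment and Informed Consent, is about the program: "they will be sent reminders to complete the program if they have not done so within the expected time frames".

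Under Secondary Outcomes, for everything except mental health literacy, "the 6-month follow-up assessment will be the primary end point as these outcomes take longer to elicit change". Secondary Hypotheses (Aim 2) instead places stigma and attitudes at posttest. Power and Recruitment allows 15% attrition, from pre- to postintervention only. Limitations and Risks says "It may be challenging to retain the participants" and answers with the short gap between pre- and posttest and with mixed models. Data Analysis assumes missing at random.

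**The concern.** Most participants are expected to do the pre-survey, program and post-survey in one sitting, so one reminder is probably enough there. An unpaid survey arriving by email half a year later is a different task, and it also gets one reminder. If that reminder reaches only people who started the survey and stopped, those who never opened the link get none.

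For outcomes measured only at baseline and 6 months, a participant who does not return the later survey contributes no post-baseline value. A mixed model keeps that person's baseline record but cannot supply the missing response. A QALY by the area-under-the-curve method needs both utility values, and contacts with services during follow-up are also reported only at 6 months. At stake are the precision of these comparisons and, if non-response relates to later distress or work loss differently by arm, their validity.

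**Working it through.** **1. What depends on the 6-month survey (Table 1)**

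- Pre, post and 6 months: GHSQ, attitudes, stigma, literacy.
- Pre and 6 months only: help-seeking behavior (hypothesis 3); PROMIS depression and anxiety, DQ5, WPAI and ReQoL-10 (hypothesis 4). Behavior, WPAI and ReQoL-10 also feed the economic analysis.

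This holds whichever section governs stigma and attitudes, since both have a posttest value.

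**2. The plan's own sample size**

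Inputs from Power and Recruitment: d = 0.2, 80% power, two-sided 0.05, ICC 0.02, 25 to 35 per workplace, 15% attrition.

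- Per arm: 2 × (1.96 + 0.84)² / 0.2², giving 393; both arms 786.
- Design effect 1 + (m − 1) × 0.02: 1.48 at m = 25, 1.68 at m = 35.
- Recruited: 786 × 1.48 / 0.85 = 1,369; 786 × 1.68 / 0.85 = 1,554.

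The stated 900 does not follow from these inputs alone. It is compatible with an unstated baseline correlation of about 0.53 to 0.62. That is a separate question and this point does not depend on it. None of the variants tried allows for loss at 6 months. I use r = 0.6 below, which is favorable to the plan.

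**3. Continuous 6-month outcomes**

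36 workplaces × 25 = 900; d = 0.2 borrowed from the primary outcome; design effect on the responding cluster size; r = 0.6 enters as a variance factor 1 − r² = 0.64. The loss rates are assumptions, because the protocol gives none.

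| Loss at 6 months | Analyzed | Power, r = 0 | Power, r = 0.6 | Detectable d at 80% power, r = 0.6 |
|---|---|---|---|---|
| 15% | 765 | 65% | 83% | 0.19 |
| 30% | 630 | 59% | 78% | 0.21 |
| 40% | 540 | 54% | 73% | 0.22 |
| 50% | 450 | 48% | 67% | 0.23 |
| 60% | 360 | 42% | 59% | 0.26 |

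Example at 30% loss: responding cluster 17.5; design effect 1 + 16.5 × 0.02 = 1.33; effective n per arm 630 / 1.33 / 2 = 237; detectable d = 2.80 × √(2/237) × 0.8 = 0.21.

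**4. Hypothesis 3**

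Limitations and Risks expects 180 of 900 with elevated symptoms. I spread them over 33 workplaces (the middle of 30 to 36), with ICC 0.02 and an assumed 30% versus 45% seeking help.

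| Loss | Remaining, both arms | Power |
|---|---|---|
| 0% | 180 | 51% |
| 30% | 180 × 0.7 = 126 | 39% |
| 40% | 180 × 0.6 = 108 | 35% |
| 50% | 180 × 0.5 = 90 | 30% |

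**5. What a better response would return**

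A gain of 5 to 10 points (assumed, not predicted) is 45 to 90 of 900, and 9 to 18 of 180. Moving from 60% to 70% response raises power from 73% to 78% in step 3 (r = 0.6) and from 35% to 39% in step 4.

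**6. When loss would bias the comparison**

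With the same loss fraction a in both arms, a simple comparison of responders is off by a × (responder-minus-non-responder gap in one arm − the same gap in the other). If the gaps are equal, the bias is zero. If they differ by 0.1 SD at 30% loss, it is 0.3 × 0.1 = 0.03 SD; by 0.2 SD at 50% loss, 0.5 × 0.2 = 0.10 SD. The documents give no information on these gaps.

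**The case against.** **Non-starters may be covered.** In the parenthesis under Trial Delivery, the verb about discontinuing attaches to the 48-hour clause. The 6-month clause gives only a time and can be read as one week after the link is sent, opened or not. Reminder time frames are also referred to Figure 1, which is not shown. This stands: a reader might infer that non-starters get no reminder, but the text is ambiguous and does not establish it.

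**Informative loss is not shown.** A reader might infer that informative loss is built into the design. The documents do not support that. Every outcome at issue is measured at baseline, and dropout explained by observed values that the model uses is compatible with missing at random. The control is time-matched, participants are blinded as far as possible, and nothing indicates that loss would differ by arm.

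**The single-sitting remark is not a rationale for one reminder.** It says only that reminders in that session should rarely be needed. Correct, and the protocol offers no separate reason for the 6-month rule.

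**The work-email problem is inferred from silence.** The article does not say what address the enrolment screen requests, and invitations may go by SMS. It cannot be called an error; asking for a lasting address is simply a cheap safeguard.

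**Other measures exist.** Access needs only an email, the survey takes 10 minutes, numbers are monitored, and attrition will be examined. These help, but none contacts a non-responder again.

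**More reminders may feel like pressure.** Coercion and Informed Consent treats perceived pressure as critical. This is a real trade-off, and it supports a small, capped number of reminders.

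**Conclusion.** The point holds as an inexpensive improvement to a rule that the protocol fixes. One reminder at 1 week, with unclear coverage of people who never open the link, is thin support for the only post-baseline measurement behind hypotheses 3 and 4 and the economic analysis, and no 6-month loss is allowed for. The posttest primary outcome is untouched.

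It would go too far to say that nearly every secondary outcome depends on this survey: Secondary Hypotheses puts stigma and attitudes at posttest while Secondary Outcomes puts them at 6 months.

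On the assumed range, going from 15% to 50% loss takes power for d = 0.2 from 83% to 67% (r = 0.6), and 50% loss takes hypothesis 3 from 51% to 30%. These figures rest on assumed loss rates, an assumed baseline correlation, the primary outcome's effect size and assumed help-seeking proportions. Hypothesis 3 has limited power for that difference even with full response, so better follow-up helps it only modestly.

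**What to change.** - For the 6-month survey, send a small fixed number of automated reminders from the research site to everyone who has not submitted it, whether or not it was opened, up to a stated closing date.
- At enrolment, ask for an email address that the participant expects still to have in 6 months.
- Keep the 48-hour reminder for the session of pre-survey, program and post-survey.
- Reconcile Secondary Hypotheses and Secondary Outcomes on the time point for stigma and attitudes.

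The cost is a website setting, one line on the enrolment screen, a few more emails per non-responder and a minor ethics amendment. Each reminder should restate that participation is voluntary. Because they come from the research site, the employer still does not learn who took part. The documents do not show how much response would rise.

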### Data Collection

#### Overview

Participants who agree to participate in the trial by clicking the link will be asked to provide an email address and complete a brief 10-minute baseline questionnaire. Following completion of the baseline questionnaire, participants will immediately be given access to the web-based program (approximately 20 minutes), which will be followed immediately by the 10-minute posttest questionnaire survey. The 10-minute follow-up survey link will be sent to participants via email 6 months after completion of their allocated condition.

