### Co-Design and Online Delivery Modes

The COVID-19 pandemic has dramatically accelerated the need for mental health programs [21], particularly those delivered distally [22]. However, few effective programs have been identified for improving help-seeking in adults [23], and existing interventions are not widely implemented to deliver public health impact [19,24]. Web-based mental health interventions are cost-effective [25] and can be widely disseminated [26], but they can have high dropout rates, increasing the need for co-design to improve acceptability [27]. There is increasing recognition of the expertise of people with lived experience of mental health problems in research, and the important insights end users of a product or service can bring to the research process, by improving translation, real-world impact, and responsive practice [28]. Co-design involves partnering with end users during all stages of designing and developing a product or service. Using this method enhances the potential that the service can be tailored to the target population, creating a strong potential to foster a sense of empowerment and ownership, which in turn may improve the uptake of and engagement with the service [27].

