### Data Analysis

An intention-to-treat approach to account for missing data of the mixed model repeated measures ANOVA (continuous data) or mixed effects logistic regression (binary data) will be used, adjusting for intraclass correlation to account for clustering effects within each site. Mixed models include all available data and account for within-individual variability, including those participants with missing data points, under the missing-at-random assumption [48].

Exploratory analyses will examine evidence for moderators or mediators of outcome and will be reported separately from the primary and secondary outcomes. Implementation outcomes at 6 months will be separately examined using description statistics, including *t* tests (2-tailed). The economic analysis will examine cost-effectiveness from the health sector and societal perspectives. The cost of the Helipad intervention and the active control program will be estimated using microcosting methods. Service use data will be limited in this study to health care professional visits or services accessed (internet program and helpline) specifically for mental health. The additional costs of health care resource use will be operationalized as the number of contacts with health professionals collected on the Actual Help-Seeking Questionnaire [49] (psychologist or counselor, psychiatrist, family doctor or GP, EAP, phone helpline, and internet-based treatment program). Lost productivity will also be evaluated in societal perspective costs as assessed through the WPAI questionnaire [47] and valued using the human capital approach. The ReQoL-10 Questionnaire [46] will be used to calculate utility values and quality-adjusted life years (QALYs) using the area under the curve method. Differences in costs between trial groups will be compared to the differences in QALYs through an incremental cost-effectiveness ratio (ICER) because of the inherent value-for-money connotations associated with cost-effectiveness ratios using QALYs. Additional ICERs using secondary outcomes will be calculated where the Helipad intervention is found to have an effect. Nonparametric bootstrapping will be used to determine CIs for ICERs.

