#### Assessments and Blinding

Table 1 presents the trial measures and assessment time points. Assessments will occur at baseline (pretest), posttest, and 6 months after the program is completed. The trial will be triple blinded. Participants will be blinded as far as possible to the condition; they will only be informed that their workplace has been randomized to receive one of two programs: (1) an enhanced interactive mental health education program or (2) a standard written psychoeducation program. We will not provide participants with information about which program is expected to be the most effective. The statistician who will perform the analyses will be blinded to condition allocation (triple blind). Finally, assessments will also be blinded, as they rely on participants independently completing self-report measures on the web.

**Table 1 table1:** Assessment time points for the Helipad cluster randomized controlled trial of a brief workplace training program to support help-seeking for mental ill-health.

Construct	Measure	Presurvey	Postsurvey	6-month follow-up survey
Gender	What is your gender?	✓		
Age	What is your age?	✓		
Language spoken at home	What language do you usually speak at home?	✓		
Ethnicity	How would you describe your ethnicity?	✓		
Education	What is the highest level of education that you have completed?	✓		
Employment status	What is your current employment status?	✓		
Industry	What industry are you employed in?	✓		
Help-seeking intentions	GHSQ^a^	✓	✓	✓
Help-seeking attitudes	ATSPPH-SF^b^	✓	✓	✓
Help-seeking behavior: service use type and quantity	AHSQ^c^	✓		✓
Mental illness stigma	(SASS^d^-modified)	✓	✓	✓
Mental health literacy	D-Lit^e^ or A-Lit^f^ composite	✓	✓	✓
Depression symptoms	PROMIS^g^ Depression-Short Form	✓		✓
Anxiety symptoms	PROMIS Anxiety-Short Form	✓		✓
General psychological distress	DQ5^h^	✓		✓
Work and activity impairment	WPAI^i^	✓		✓
Quality of life	ReQoL-10^j^	✓		✓
Adverse events	Did you have any unexpected or negative experiences that might be related to completing this program?		✓	✓
Intervention acceptability	AIM^k^		✓	
Intervention appropriateness	IAM^l^		✓	
Intervention feasibility	FIM^m^		✓	
Debriefing	Explanation of study			✓
Interview	Interest in an interview		✓	

^a^GHSQ: General Help-Seeking Questionnaire.

^b^ATSPPH-SF: Attitudes Toward Seeking Professional Psychological Help Scale-short form.

^c^AHSQ: Actual Help-Seeking Questionnaire.

^d^SASS: Stigma and Self-Stigma Scales.

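### As written, a participant who does not finish the program has no 6-month survey date and no described route to the posttest, so non-completion becomes missing outcome data

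*Protocol article*

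**What the plan says.** Two places in the protocol article anchor the last assessment to program completion. The Overview under Data Collection says: "The 10-minute follow-up survey link will be sent to participants via email 6 months after completion of their allocated condition". Assessments and Blinding says: "Assessments will occur at baseline (pretest), posttest, and 6 months after the program is completed". Neither gives a date for a person who does not complete.

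The same Overview places the program directly after baseline, "which will be followed immediately by the 10-minute posttest questionnaire survey". That posttest is the primary end point.

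For people who break off, Participant Recruitment and Informed Consent lets them "re-enter the survey or program at the last point they left off". Trial Delivery adds one reminder, at 48 hours for anything up to the posttest, with a link "to continue from where they left to complete that part of the study". No link that skips the rest of the program is described.

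Data Analysis promises "An intention-to-treat approach to account for missing data", using mixed models with all available data under missing at random.

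**The concern.** The Estimand section asks about workplace employees, with no restriction to those who finish. If outcomes are requested only from people who finish, the post-baseline comparison rests almost wholly on them, and finishing happens after randomisation.

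There is reason to think finishing could differ by arm. Helipad uses videos, quizzes and clickable diagrams and was kept short to help people complete it. The control is written text with little interaction. The Introduction says of web-based mental health interventions in general that "they can have high dropout rates, increasing the need for co-design to improve acceptability". The arms therefore differ in the feature expected to drive completion.

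This is a rule about whom to ask, so it cannot be left to an analysis plan: answers that were never requested cannot be recovered later. It also touches safety. Table 1 asks about adverse events only at posttest and 6 months, so a person who stops because the content is upsetting might never be asked.

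**Working it through.** **Step 1. Follow three participants through the described flow.**

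- *Finishes program and posttest:* has a posttest and a completion date, and is sent the 6-month link.
- *Finishes program, skips posttest:* has no posttest unless the reminder works, but has a completion date and is sent the 6-month link.
- *Completes baseline, stops during the program:* is returned to the stopping point by the reminder. If they do not resume, no route to the posttest is described, there is no completion date, and so there is no 6-month link.

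Only the third person loses every post-baseline measurement.

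**Step 2. Which outcomes depend on this (Table 1).**

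- Baseline and 6 months only: help-seeking behavior, depression, anxiety, distress, work and activity impairment, and quality of life. These include the inputs to costs and QALYs. The problem is clearest here, because the 6-month timing is stated outright.
- Baseline, posttest and 6 months: help-seeking intentions (primary), attitudes, stigma and literacy. For the posttest, the gap is inferred from the sequence.
- Posttest and 6 months only: adverse events.

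**Step 3. How many people.** Inputs from Power and Recruitment: 900 recruited, 15% attrition from pre- to postintervention.

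- No posttest: 0.15 × 900 = 135. With posttest: 900 − 135 = 765.
- The 15% is attrition, not non-completion. It mixes the second and third participants of Step 1, and the implementation measures section lists completion and attrition separately. So 135 is the most that could lack all post-baseline data under this assumption.

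**Step 4. What it could do to the estimate (illustration; all inputs except the 0.2 target are assumed).** Let p be the proportion not completing in an arm, and g the gap in outcome between completers and non-completers that remains after arm and baseline score are taken into account, equal in both arms. The completers' mean overstates the arm mean by p × g, so the between-arm bias is g × (difference in p).

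- g = 0 (missing at random holds): bias 0, whatever the difference in p.
- g = 0.2 SD, difference 5 points: 0.2 × 0.05 = 0.01 SD. Difference 10 points: 0.2 × 0.10 = 0.02 SD.
- g = 0.5 SD, difference 5 points: 0.5 × 0.05 = 0.025 SD. Difference 10 points (such as 10% against 20%): 0.5 × 0.10 = 0.05 SD.

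The last value is 0.05 / 0.2 = one quarter of the target effect. If the control arm loses more, the Helipad effect is understated; if Helipad loses more, it is overstated.

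Equal non-completion does not remove the issue. Suppose completers gain 0.2 SD and non-completers gain nothing. The effect in everyone is 0.2 × (1 − p): 0.19 at 5% (45 people), 0.17 at 15% (135) and 0.14 at 30% (270). A model informed only by completers would still point to 0.2.

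**The case against.** No sentence says that non-completers are refused the posttest or the 6-month survey. Completion may be only a convenient timing anchor. Trial Delivery expects some people to break off and describes a way to reconnect them. The flowchart, to which the recruitment section refers for time frames, is not shown, and a condensed article may omit the email rule for this group. This stands as a reason for caution: the exclusion is a literal reading, not a stated policy.

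A reader might infer more: that the trial is a completer analysis, that intention-to-treat is not delivered, or that randomisation is broken for the primary outcome. The document does not support that. No completer or per-protocol population is defined, nothing moves participants out of their allocated arm, and baseline data from people who stop can enter the mixed model. Completion that differs by arm is also compatible with missing at random, since arm and baseline score are observed. The assumption fails only if stopping depends on unobserved outcomes beyond those.

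The setting limits the size as well. Most people are expected to do baseline, program and posttest in one 40-minute sitting, and retention is acknowledged as a risk. Someone who abandons a 20-minute program and ignores a reminder may not answer a posttest link either.

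This narrows the point but does not remove it. The completion-based timing is stated twice, no alternative date is given, and reconnecting people means returning them to the program.

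**Conclusion.** The point holds in a limited form. Under the described procedures, not finishing the program amounts to missing outcome data. The intention-to-treat result then depends on an untestable missing-at-random assumption, with almost nothing observed after baseline among those who stop. The evidence is firmest for the 6-month outcomes, the economic evaluation and 6-month adverse-event reporting. It is weaker for the primary posttest, where the route is inferred.

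The number affected is at most 135 of 900 at the protocol's own attrition assumption. Any bias is unknown: zero if missing at random holds, and 0.01 to 0.05 SD across the assumed inputs above. These figures show scale only and do not predict bias in this trial. The wording should be corrected before the survey schedule is in use, because follow-up that is not requested is lost.

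**What to change.** 1. Send the 6-month survey to every participant who completed baseline, timed from baseline completion and regardless of program completion. State this in both the Overview and Assessments and Blinding.
2. For people who stopped the program, add a direct posttest link to the 48-hour reminder, beside the link that resumes the program.
3. State that all baseline completers are analysed by the arm to which their workplace was allocated.

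If the website already follows non-completers, it is enough to say so and to give the date that starts their 6 months.

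The cost is a changed email trigger, one extra link and a few lines of text. Email addresses are already collected before baseline. For people who finish in one sitting, baseline and program completion fall on the same day, so their schedule does not move. The downsides are that some posttests will reflect partial exposure, and that the rise in posttest response may be modest. The gain at 6 months is surer, since people who would not have been contacted will at least be asked.
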